### Study intervention

The first phase of the GHI, a three-year (2018–2020) programme funded by Bayer AG and implemented through the GIZ, was designed to improve risk assessment and management of hypertension and CVD in public health facilities and hospitals in the GAR. Its primary objective was to improve prevention, detection or diagnosis, and management of CVD. The GHI includes five main components: (i) Stakeholder engagement and development of national guidelines for the management of CVD, (available in hard copies and a digital app); (ii) Training of healthcare workers coupled with coaching / mentorship visits; (iii) Equipment supplies for the diagnosis and treatment of CVD; (iv) Training of healthcare workers for the collection of facility-level data for programme monitoring and the GHI programme team worked with the Policy, Planning, Monitoring and Evaluation Division of the GHS to include important NCD indicators including CVD in the District Health Information Management System (DHIMS2) to facilitate facility-level routine data collection and reporting; and (v) Establishment of a round the clock (“24/7”) CVD support center.

### Conceptual framework

In line with the abovementioned implementation science approach and the aforementioned research questions, our study adopts the RE-AIM framework as the guiding operational evaluation framework. The RE-AIM framework offers a comprehensive structure that will guide the quantitative and qualitative data collection to systematically evaluate the robustness of the intervention (“the GHI”) across the RE-AIM domains – reach, effectiveness, adoption, implementation, and maintenance as well as related costs, and the potential for scaling up the intervention to other regions in Ghana [22]. It should be noted, that within the effectiveness domain, some of the indicators may have elements to estimate impact, where we hope to carry out a Difference-in-Difference (DID) analysis and if routine health data is available an interrupted time series-analysis (ITSA) enabling a quasi-experiment to attribute causality to the intervention.

The Theory of Change (ToC) development was informed by a discussion with stakeholders of how the intervention (“the GHI”) induced changes in the management of hypertension and CVD care in a “real-world setting”, a description of the health systems pathway through which this change was expected to happen, and the RE-AIM evaluation framework to assess whether and how change has happened [23] [24].

Considering the content of our intervention specifically, we turned to the World Health Organization’s (WHO) six health system building blocks (HSBB) to structure our work [25]. We did so out of a desire to analyze systematically how the actions carried out by the GHI had produced effects on each of the six HSBB. The WHO HSBB at health facilities enables a comprehensive evaluation of the health system performance, clinical, processes of care and quality of care outcomes. Further, understanding implementation outcomes (fidelity, acceptability, and effectiveness) of the intervention using a conceptual ToC model from diverse user’s perspectives can support consideration of how and why the intervention is likely to generate the changes observed and assist in thinking through the potential for the expansion and scale-up of the GHI in contextually similar settings. It may also contribute to consideration of how to manage implementation over time and highlight factors that are likely to support the sustainability and achievement of long-term goals of the GHI.

To ensure measures of patient experience of healthcare quality are valid (measuring what they intend to) they need to capture a wide array of domains. Since the core of the GHI focused on enhancing service delivery models, we further integrated the widely accepted six domains of health care quality by the Institute of Medicine (IOM) into our conceptual framework. We thus, look at the six domains; care which is Safe, Timely, Effi cient, Effective, Equitable and Patient-centered, referred to as ‘STEEEP’ [26]. Taking ‘timely’ as an example; in an outpatient setting, timely might be the length of time a patient has to wait for his/her CVD consultation, whereas in a hospital setting, it may be interpreted as the length of the time the patient has waited for a diagnostic test.

The major activities that the GHI focused on are all believed to support the health system attain its mission and vision: quality health service delivery, leadership and governance, and capacity building of the health workforce. Thus, evaluation of the overall Ghanaian healthcare system in the context of implementing the intervention using the HSBB (service delivery, health workforce, medicines/vaccines and technology; health information systems; financing; and leadership/governance) is required to identify gaps as well as provide insights to further scale up and sustain the activities of the GHI across Ghana. In this evaluation, emphasis is placed on the interaction and interdependence across and within building blocks from a health system perspective. We will also look at how the demand side of health services (community and patients) interacts with the intervention components given the context in which the intervention is being implemented and to assess effectiveness, safety, and timeliness of patient-centered care. We hope to demonstrate the pathways through which the GHI operates to achieve the desired outcomes (i.e., improvements in screening, diagnosis and control of hypertension and CVD).

Figure 2 provides a visual illustration of our conceptual framework while Fig. 3 outlines the specific research questions addressed under each dimension of the RE-AIM framework, being informed by the conceptual understanding of the HSBB and the IOM’s STEEEP quality framework described above.

### Study design

This study adopts a triangulation mixed- and multi-methods quasi-experimental design. A triangulation mixed methods design employs quantitative and qualitative methods in parallel, holding equal weight within a given research context, and appraised jointly to understand complex phenomena and changes. In this case, the authors investigate changes inducted by the GHI. A multi-method design involves multiple sources of data collection and/or relies on multiple analytical strategies, within each strain of work, the quantitative and the qualitative. The evaluation research protocol development was informed by wide consultation, including review by the research teams at the University of Ghana Medical School, Ghana, and the Heidelberg Institute of Global Health (HIGH), Germany. Researchers took part in a study design workshop in Accra in April 2022. In addition, between April and July 2022, multiple virtual meetings were organized to agree on the final study design and data collection protocol.

### Study components

This is a facility-based study, meaning that, with the exception of the interviews with policy makers and mid to high-level health system offi cers, all other data collection activities take place at the facility level. In all participating health facilities, we implement multiple data collection tools: (1) Health facility survey; (2) Healthcare provider survey to assess knowledge, attitudes, and practices (KAP) on hypertension and CVD; (3) Patient exit survey; and (5) Medical record review (MRR) before and after implementing the GHI. In addition to primary data collection, the study also relies on secondary routine health system data obtained by the study team in fully anonymized format, the DHIMS2. Figure 4 provides a summary of the health service delivery evaluation domains, measures, or indicators (process, outcomes, and sustainability), and tools.

### Quantitative study component

For the assessment of the health service delivery performance between the intervention and control facilities, we are utilising mixed methods and multiple survey tools. Individual methods are chosen strategically based on the research question as well as considering feasibility and practicality [27]. Data is being collected at the facility-, provider- and patient-level using multiple surveys:

**Health facility assessment survey**: to determine the existing infrastructure, human resources, availability of services for hypertension and CVD, availability of laboratory tests and diagnostics, medicines for hypertension and CVD treatment and health service delivery indicators related to hypertension and CVD.**Provider survey**: to examine the knowledge, attitudes, and practices (KAP) regarding CVD and hypertension management as well as the acceptability of the GHI from provider’s perspective in intervention facilities only.**Patient exit survey**: patients asked post-consultation about the provision of care in the consultation to assess patient experiences and satisfaction with the hypertension or CVD related care received at the intervention and control facilities.**Medical record review**: before and after the implementation of the GHI to assess differences in hypertension and CVD care practices between intervention and control facilities.

For the provider KAP survey and exit survey, the field data collection team(s) visit a health facility and capture a random sample of healthcare providers and patients available on the day of the visit. This method relies on random sampling and the effi ciency of the field team. In essence this means maximizing the number of potential respondents to be interviewed on the day of the visit i.e. all eligible patients exiting the facility are interviewed, all eligible healthcare providers present and available at the facility are interviewed [28] [29]. The field work is carefully timed so that it coincides with the day of a hypertension / CVD clinic. Prespecified **eligibility criteria** is applied for health facilities and study participants (providers and patients) for the quantitative evaluation. The health facility assessment survey is carried out in all GHI intervention facilities, and matched control health facilities to specific characteristics (example, level of care, volume of patients attending the clinic, bed size, human resources available, etc.). The provider survey is recruiting providers (doctors, nurses, physician assistants, pharmacists) aged 18 years and above, both males and females; presently working in the facility at least from the last 3 months. Further, a licensed provider is defined as a physician or a nurse, pharmacist or physician assistant who is directly involved in providing CVD related services (counseling, health education, or consultation services or pharmacological therapy). The provider survey excludes those healthcare workers who have a managerial position and do not provide any patient care. Also, a physician, nurse or pharmacist who has worked in the facility for less than 3 months is excluded from the provider survey. The patient exit survey is carried out among those aged 18 years, both males and females, and having physician diagnosis of hypertension or other CVD conditions. The exclusion criteria include patients having diseases associated with frequent hospitalization (advanced cancer, end stage renal disease) bedridden or debilitating conditions. The MRR is performed for the patient folders for those aged 18 years and above, both males and females, and having physician diagnosis of hypertension or CVD conditions-Medical records from 2018 to 2022 are being reviewed. The medical records of pregnant women and those patients having diseases associated with frequent hospitalization (advanced cancer, end stage renal disease); bedridden or debilitating conditions are excluded for the MRR.

### Data collection Tools, Indicators, and Strategies

The quantitative evaluation component is critical to learning whether intervention improves outcomes among patients seeking care for hypertension and CVD in health care facilities. This component includes the following sets of quantitative tools, specifically:

**Facility based structured survey**, including analysis of facility registries & clinical records, to capture indicators of quality-of-service delivery (input, process, outcome).**Interviews with healthcare providers** to assess the knowledge, attitude, and practice regarding hypertension and CVD.**Exit interviews with the patient** to assess the client’s perception of the CVD consultation or examination, as well as his / her recollection of the instructions that he / she received about treatment or preventative behaviour.**Review of medical records** to capture indicators of quality-of-service delivery before and after GHI implementation.**Health management information systems** data with data being aggregated monthly at facility level for each of the CVD outcomes of interest.

The rationale for selecting service delivery, processes of care, clinical and quality of care indicators are based on the aspirations to achieving optimal health service performance and to guide the health care planning as a continuous quality improvement tool to drive health service improvement and better health outcomes [30] [31]. The outcome indicators are chosen from the recommendations of the national and international guidelines focused on CVD as well as to reflect how the facility or provider level determinants affect individual health behaviour and wellbeing (Table 1).

The exit survey draws questions from previous patient exit and household surveys and were further adapted to fit the Ghanaian context. Demographic and socioeconomic questions were based on the Ghana Census and Demographic and Health Survey. The exit interviews with the patient examines the respondent’s perception of the CVD consultation or examination, as well as his/her recollection of the instructions that he/she received about treatment or self-care behavior. The survey also captures how patients perceive the quality of specific aspects of the health facility and its providers. Patients are asked to rate 27 aspects of the facility visit on a five-point Likert scale with related Emoji’s.

The medical records of outpatient and inpatient folders at two cross-sectional timepoints before and after GHI implementation are being reviewed to assess between group differences in hypertension and CVD care delivery. Eligibility of medical records are pre-specified based on confirmed diagnosis of hypertension or CVD, and complete medical records with at least data available on patient demographics (age, sex), medical history (confirmed case of hypertension or CVD), laboratory results (any test prescribed, or test reports reviewed), and medical treatment or prescription.

Lastly, DHIMS2 data routinely collected by the MoH in Ghana to monitor service provision consisting of monthly facility-specific counts for a wide range of services, including CVD will be analyzed to assess the differences in care delivery between the intervention and control health facilities over the time period. In line with prior work, to translate monthly counts into indicators that adequately capture service coverage, we construct outcome variables that account for the underlying target population living in the catchment area of a given facility [32]. More specifically, we apply interrupted time series analysis to DHIMS2 data to assess impact on the following CVD indicators: prevalence of hypertension, coronary heart disease, stroke, heart failure and related mortality.

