### Study outcomes

The primary outcome measures being assessed between the intervention and control facilities are: i) proportion of screened individuals for hypertension, ii) newly diagnosed patients with hypertension or CVD, iii) prescription of guideline directed medical therapy for hypertension and CVD, iv) BP control defined as < 140/90 mmHg, v) provider knowledge and practice related to hypertension and CVD and vi) patient centered care and satisfaction. The study also assesses several secondary outcome measures including difference in total waiting time for physician consultation and physician acceptability of the GHI.

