### Sample size

The sample size of 1,200 participants in total for the MRR or patient exit survey will provide 90% power to detect 10% relative difference between the intervention and control facilities in processes of care indicators such as prescription of evidence-based therapies and blood pressure control. at an α = 0.05 and accounting for 20% non-response rate or missing data.

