### Statistical analysis

Quantitative data is analyzed by descriptive statistics for demographic, socio-economic and other patient-, provider- and health system level factors between the intervention and control facilities. Differences in service delivery indicators, process of care measures (prescription of guideline directed medical therapy) and clinical outcomes (BP control) will be compared between the intervention and control facilities. The chi-square test is used to evaluate differences between categorical variables. Two-sided p-values < 0.05 will be considered statistically significant. Composite performance scores are defined by determining the proportion of patients who receive concordant care compared to patients who receive discordant care between the intervention and control facilities. Linear and logistic regression analysis techniques are used to assess determinants of health outcomes, processes of care measures, and treatment satisfaction [33]. Random-effects regression analyses will be used to account for cluster effects and imbalances between intervention and control group health facilities; Effect sizes will be presented as risk ratios for binary outcomes, and as mean differences for continuous outcomes; 95% confidence intervals (CI) will be given for both. Missing data in outcome measures will be handled by appropriate imputation methods.

A propensity score will also be created using logistic regression and will contain those variables associated with treatment at a health facility [34]. Analysis of clinical outcomes analysis will also use ANCOVA (analysis of covariance) to compare the prescription of evidence-based medicines, and mean change in BP and lipids between the intervention and control arm facilities [29]. Other outcome measures such as behavioural and biochemical risk factors will be analyzed using logistic or conditional logistic regression to adjust the comparisons for other variables. We shall also compare the percentages achieving clinical and behavioural targets between the intervention and control arm facilities.

The fidelity analysis will uncover the extent to which the GHI was fully or partially implemented by various health system stakeholders.

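### Medical record review admits only folders with treatment data, so diagnosed patients with no recorded treatment leave the denominator for prescribing and BP control

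*Protocol article*

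**What the plan says.** Under Data collection Tools, Indicators, and Strategies, eligibility for the medical record review requires a confirmed diagnosis and "complete medical records with at least data available on patient demographics", medical history, "laboratory results (any test prescribed, or test reports reviewed), and medical treatment or prescription".

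Under Quantitative study component, the same review is described with a wider entry rule: adults with a physician diagnosis, records from 2018 to 2022, and exclusions for pregnancy and certain severe conditions. No completeness condition appears there. That section gives the review's purpose as a before-and-after comparison "to assess differences in hypertension and CVD care practices between intervention and control facilities".

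Study outcomes lists, among six primary outcomes, (iii) "prescription of guideline directed medical therapy for hypertension and CVD" and (iv) "BP control defined as < 140/90 mmHg". The Sample size section sizes the record review or the exit survey on indicators of these two kinds.

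**The concern.** A diagnosed patient with nothing prescribed has failed outcome (iii). If the folder must contain treatment data before it is abstracted, that failure never reaches the denominator. The review then estimates how often treated patients receive guideline therapy. It does not estimate how often diagnosed patients do.

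Starting treatment in untreated patients is one obvious route by which training, guidelines and equipment could work, and this filter makes that route invisible. BP control is affected too if untreated patients are less often controlled.

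The planned analysis cannot repair this. Imputation, propensity scores and random-effects models all operate on folders already admitted. The before-and-after comparison does not help either. If GHI raises only the share treated, and only in intervention facilities after implementation, guideline concordance among treated patients is the same in all four arm-by-period cells, and a difference-in-differences on eligible folders is zero.

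**Working it through.** The plan gives no figure for the share of diagnosed patients with recorded treatment, or for guideline concordance among them, so there is no stated figure to reproduce. All rates below are assumptions, and the 1,200 sample size does not enter.

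**Notation.** a = share of diagnosed patients with any recorded treatment. g = share of those whose therapy is guideline-directed. I = intervention, C = control. The treatment condition is taken as the only one that binds.

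- Rate among all diagnosed patients: a × g.
- Rate among eligible folders: g. Each arm's rate is inflated by the factor 1/a.
- True RR = (a_I × g_I)/(a_C × g_C). RR among eligible folders = g_I/g_C = true RR × (a_C/a_I).

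The distortion of the risk ratio is therefore exactly a_C/a_I.

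**Main illustration.** a = 0.85 vs 0.70, g = 0.60 in both arms. All diagnosed: 0.85 × 0.60 = 0.51 vs 0.70 × 0.60 = 0.42, RR 0.51/0.42 = 1.21. Eligible folders: 0.60/0.60 = 1.00.

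**Range of cases (intervention vs control).**

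| a | g | All diagnosed | True RR | RR in eligible folders |
|---|---|---|---|---|
| 0.85 vs 0.70 | 0.60 vs 0.60 | 0.51 vs 0.42 | 1.21 | 1.00 |
| 0.70 vs 0.60 | 0.80 vs 0.70 | 0.56 vs 0.42 | 1.33 | 1.14 |
| 0.80 vs 0.60 | 0.65 vs 0.70 | 0.52 vs 0.42 | 1.24 | 0.93 |
| 0.70 vs 0.70 | 0.77 vs 0.70 | 0.539 vs 0.49 | 1.10 | 1.10 |

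The effect can vanish, shrink, reverse or be left intact on the ratio scale. If recorded treatment were less common in intervention folders, a_C/a_I would exceed 1 and the ratio would be overstated.

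**BP control.** Assume 40% controlled if treated, 10% if untreated, and a = 0.80 vs 0.60. All diagnosed: 0.80 × 0.40 + 0.20 × 0.10 = 0.34 vs 0.60 × 0.40 + 0.40 × 0.10 = 0.28, RR 1.21. Eligible folders: 0.40 vs 0.40, RR 1.00.

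**The case against.** Several stronger readings are tempting, and the document does not support them.

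- *The rule selects on the primary outcome itself.* It does not. The filter asks for any treatment; the outcome is guideline-directed therapy. An eligible folder can still fail, and an effect on choice of therapy survives.
- *A laboratory result is required, and this is also selection on a primary outcome.* A test that was merely ordered meets the condition, and testing is not one of the six primary outcomes.
- *GHI changes who passes the filter.* This is plausible but not shown. The data-collection training under Study intervention concerns facility-level programme monitoring and routine reporting, not documentation in patient folders.
- *The rule contradicts the missing-data provisions.* A reader might set it against "Missing data in outcome measures will be handled by appropriate imputation methods" and "accounting for 20% non-response rate or missing data". There is no conflict. BP and lipid values are not in the required minimum, so they can be missing in eligible folders, and the 20% also covers exit-survey non-response.

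Two objections carry weight. First, having data on treatment could mean that the treatment field is filled in, including an explicit entry of no treatment. The bias would then be smaller, but the text does not say this, and folders that are simply silent on treatment would still be excluded. Second, other sources exist. Table 1 assigns prescribing and BP below 140/90 to the health facility survey, DHIMS2 and the exit survey, and exit-survey eligibility has no completeness condition. That confines the point to outcomes taken from the record review. It does not remove it, because the review has its own stated purpose of comparing care practices before and after GHI.

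**Conclusion.** The point holds for outcomes derived from the medical record review, chiefly prescribing and BP control. Taken literally, the rule drops diagnosed patients with no recorded treatment, inflates prescribing rates by 1/a in each arm, and multiplies the risk ratio by a_C/a_I.

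A reader might infer that the GHI effect will be erased. The document does not support that. Complete loss of the effect, as in 1.21 becoming 1.00, requires equal concordance in both arms, and equal shares with recorded treatment leave the risk ratio unbiased. Every rate used here is assumed, so neither size nor direction can be fixed from the document. What can be said is that the rule hides one plausible route of benefit, and that no planned analysis can restore it without the excluded folders.

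**What to change.** - Define record-review eligibility as under Quantitative study component: age, confirmed diagnosis, review window and clinical exclusions. Drop the laboratory and treatment completeness condition.
- In the main prescribing analysis, keep diagnosed folders with no recorded treatment in the denominator as not prescribed. Report the complete-record analysis as a sensitivity analysis.
- Report the number of folders lacking treatment or test data by arm and period. If screening has already been done, report the rejected folders the same way where they were logged.

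**Cost.** The rule itself is a wording change. The article describes the review as under way, so retrieving folders already rejected would be extra fieldwork. There will be fewer usable BP and lipid values per 1,200 records.

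There is also a statistical price. Scoring silence as no prescription treats poor documentation as poor care. If the 85% vs 70% in the illustration reflected better recording alone, with no difference in treatment, the true ratio would be 1.00 and the main analysis would report 1.21. That is why both analyses and the completeness counts should be shown together.
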